### Objectives

The primary objectives of this study are given below.

First, this study aims to measure the monthly rate and the number (proportion) of individuals with APRI greater than 1.0 and FIB-4 greater than 2.67 among people who undergo automated APRI and FIB-4 calculation on blood test events performed through a single Australian pathology service.

Second, this study aims to measure the monthly rate of transient elastography referrals received after the introduction of automated APRI and FIB-4 reporting, compared with the preintervention period.

Third, this study aims to measure the monthly rate and the number (proportion) of transient elastography tests performed in those with an elevated APRI and or FIB-4 score during the intervention period, compared with the preintervention period.

Fourth, this study aims to measure the monthly rate and the number (proportion) of individuals with APRI greater than 1.0 or FIB-4 greater than 2.67 that have cirrhosis range median stiffness (kPa) confirmed on FibroScan.

Finally, this study aims to measure the number (proportion) of individuals with cirrhosis range FibroScan during the intervention period that is linked to specialist care, compared with the preintervention period.

The secondary objective of this study is to describe the sociodemographic factors associated with (1) APRI greater than 1.0 and FIB-4 greater than 2.67, (2) attendance at FibroScan appointment, (3) cirrhosis diagnosed on FibroScan, and (4) linkage to specialist care.

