### Statistical Analysis Plan

#### Outcome Measures

Data will be analyzed per test event and per individual tested.

Primary outcomes of this study include the number of APRI and FIB-4 scores calculated on blood test events conducted during the study period, overall and per month; the number (proportion) of APRI scores that are greater than 1.0 and FIB-4 scores that are greater than 2.67; number of FibroScan referrals overall and per month, operationalized as number of completed FibroScan referrals generated online using the recommended St Vincent’s Pathology FibroScan referral link on the request slip, or St Vincent’s Pathology APRI or FIB-4 calculation web page referral form link; number of individuals with an APRI greater than 1.0 or FIB-4 score greater than 2.67 who undergo a FibroScan test at St Vincent’s Hospital Melbourne overall and per month; proportion of individuals with an APRI greater than 1.0 or FIB-4 score greater than 2.67 who undergo a FibroScan test at St Vincent’s Hospital Melbourne; the number of individuals per month who undergo FibroScan at St Vincent’s Hospital Melbourne who have cirrhosis diagnosed (liver stiffness measurement >12.5kPa); the number (proportion) of individuals with an APRI greater than 1.0 or FIB-4 score greater than 2.67 who have cirrhosis confirmed by FibroScan; the number (proportion) of individuals with etiology-specific cirrhosis range FibroScan results that are referred to the specialist liver clinic; and the number (proportion) of individuals with etiology-specific cirrhosis range FibroScan results that attend to the specialist liver clinic appointment.

The secondary outcomes of this study include the number (proportion) of individuals, stratified by age category, sex, and postcode who have elevated APRI greater than 1.0 and FIB-4 score greater than 2.67, attend the FibroScan clinic for further testing, have etiology-specific cirrhosis range FibroScan scores (kPa), and attend a liver specialist clinic appointment.

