### Analysis Methods

The number of APRI and FIB-4 scores generated and the proportion of APRI and FIB-4 scores in the cirrhosis range will be described overall and rates per month will be calculated.

The number (proportion) of individuals with an elevated APRI or FIB-4 who are referred for a FibroScan will be described overall and per month; and the number of FibroScan referrals after the intervention will be compared with the number of FibroScan referrals prior to the intervention by logistic regression modeling (time series analysis with the timepoint of interruption defined as February 1, 2024, when the reported APRI score intervention was introduced).

Similarly, the number (proportion) of individuals with an elevated APRI or FIB-4 who are referred for a FibroScan and who attend their FibroScan appointment, overall and per month, will be described and compared with the number (proportion) of FibroScan appointments attended prior to intervention using linear regression modeling, as well as the number (proportion) of individuals with FibroScan results in cirrhosis range that are referred and attend specialist liver clinic appointments.

The number and proportion of individuals with an elevated APRI or FIB-4 who had cirrhosis confirmed by FibroScan will be described, and sensitivity, specificity, and positive and negative predictive values of APRI for cirrhosis determined by confusion matrix. The area under the receiver operating characteristic curve of APRI and FIB-4 for cirrhosis diagnosis will also be calculated by receiver operating characteristic analysis.

The bivariate distribution of sociodemographic (sex, age category, and urban or regional place of residence [defined by postcode using SEIS data]) and clinical variables (liver disease indication) within the proportion of people with elevated APRI and FIB-4 score, who attend FibroScan testing, have elevated FibroScan results, and attend the liver specialist clinic will be determined and compared with their counterparts using chi-square test for categorical data, 2-tailed Student *t* test for parametric continuous data, and Wilcoxon rank-sum test for nonparametric continuous data as appropriate.

A 2-tailed *P* value of .05 will be used as the significance threshold for all analyses. All analyses will be performed using STATA (version 17; Stata Corporation).

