### Sample Size Justification

We have conducted a preliminary analysis of the number of AST and platelet count testing events that were performed at St Vincent’s Pathology over a 12-month period (2019). These data showed approximately 11,000 people known to St Vincent’s hospital clinics, and a further 4400 people in the community that had AST and platelet count testing events, that would have allowed APRI calculation to be performed, proving the feasibility of reaching large numbers within the community for cirrhosis screening.

For the comparison of rate of referral for FibroScan before and after the intervention, we estimate that we will be powered to detect a 10% difference in rates of FibroScan referral before and after the intervention. For the logistic regression analyses to determine the difference in proportion of APRI scores leading to referral before and after providing cirrhosis information and FibroScan referral link information (overall and by subgroup), and for determining the proportion of FibroScan referrals that are attended (overall and by subgroup), we are powered to detect a 5% or greater difference between the intervention and historical control groups with power 90% and a sample size of 1100 per subgroup. The above numbers of more than 15,400 individuals having APRI calculations within 12 months suggest that we will be adequately powered to explore our end points including stratified by sex, urban versus rural place of residence, age category, socioeconomic quartile of place of residence, and indication for FibroScan (all of which are expected to have >1000 individuals in each subgroup).

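### Logistic regression is named for a before-after comparison of monthly referral counts, which it cannot model, and the power section assumes different outcomes and, apparently, a different attendance model

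*Protocol article*

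**What the plan says.** Five places in the protocol article bear on this.

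- **Objectives.** The referral objective is a monthly rate: "this study aims to measure the monthly rate of transient elastography referrals received after the introduction of automated APRI and FIB-4 reporting", against the preintervention period.
- **Outcome Measures.** The outcome is a count without a denominator: "number of FibroScan referrals overall and per month, operationalized as number of completed FibroScan referrals generated online" through the pathology service's link or web page.
- **Analysis Methods, referrals.** The break in the series is placed at the first day of February 2024. The proportion of people with elevated scores who are referred is to be described. The number of referrals is what gets compared: it "will be compared with the number of FibroScan referrals prior to the intervention by logistic regression modeling (time series analysis".
- **Analysis Methods, attendance.** Attendance is to be "compared with the number (proportion) of FibroScan appointments attended prior to intervention using linear regression modeling".
- **Sample Size Justification.** For the rate comparison the authors estimate that "we will be powered to detect a 10% difference in rates of FibroScan referral before and after the intervention", with no model, baseline or scale. A separate sentence on logistic regression covers the proportion of APRI scores leading to referral, continues "and for determining the proportion of FibroScan referrals that are attended", and gives 90% power for a difference of 5% or more with 1100 per subgroup.

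**The concern.** The number of referrals in a month has no yes/no form, so a logistic model has nothing to fit unless the outcome is redefined as referred or not referred among a stated set of people. The sentence does not do that, and the referral count in Outcome Measures is not restricted to people with elevated scores. Whoever runs the analysis will have to change either the model or the outcome, possibly after seeing the data, for one of the main before-after comparisons.

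The power statement does not settle the choice, because it rests on a proportion rather than a count and apparently on a different attendance model. A comparison of raw numbers would also read a change in testing volume as an effect of reporting. Such a change is plausible: scores appear only when AST, ALT and platelets are requested together, and clinicians are told of the new reporting about a month beforehand.

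**Working it through.** **1. Outcome and model, side by side.**

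| Outcome | Objectives / Outcome Measures | Analysis Methods | Sample Size Justification |
|---|---|---|---|
| Referral | monthly rate or count | number, logistic, time series | (a) rate, no model; (b) proportion of APRI scores, logistic |
| Attendance | number and proportion | number (proportion), linear | proportion, in the logistic sentence |

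For referral the model name agrees with (b), but the outcome scale does not. For attendance the scale can agree, but the model name apparently does not. A trial logit fit to 12 simulated monthly counts stopped with an error, because the response must lie between 0 and 1.

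**2. What the 1100 corresponds to.** Inputs: two-sided 0.05, power 0.90, difference 5% read as percentage points (assumption), two equal groups. No baseline is given, so the figure cannot be reproduced from the stated inputs alone.

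n = [1.960·√(2p̄(1−p̄)) + 1.2816·√(p₁(1−p₁) + p₂(1−p₂))]² / (p₂−p₁)²

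For 13% against 18%, p̄ = 0.155: [1.960·√0.26195 + 1.2816·√0.2607]² / 0.0025 = 1,099 per group. Other baselines:

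| Baseline | n per group, 90% power | Power with 1100 per group |
|---|---|---|
| 5% | 582 | 99% |
| 10% | 918 | 94% |
| 13% | 1,099 | 90% |
| 20% | 1,464 | 80% |
| 50% | 2,095 | 65% |
| 80% | 1,212 | 87% |

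The figure fits a baseline near 13%, or the mirror near 82%. It is a calculation for a binary proportion and does not carry over to a series of counts.

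**3. The rate comparison as a count.** Assumptions: 10% means a rate ratio of 1.10, equal six-month periods, Poisson counts without overdispersion, no trend term. With m preintervention referrals, the variance of the log rate ratio is 1/m + 1/(1.1m), so

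m = (z₁ + z₂)²·(1 + 1/1.1) / (ln 1.1)², where z₁ is the two-sided 5% point and z₂ the power point.

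- 80% power: 7.849 × 1.9091 / 0.009084 = 1,650
- 90% power: 10.507 × 1.9091 / 0.009084 = 2,209 (rounded up)

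Overdispersion or a trend term would raise both. The article gives no referral volumes, so the claim for the rate comparison can be neither confirmed nor refuted.

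**4. Testing volume.** Expected referrals = people tested × referrals per person tested. If 10% more people are tested and the second factor is unchanged, referrals rise by 1.10 × 1.00 = 1.10. Under the relative reading, that equals the difference the study says it can detect.

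**5. Is linear regression of attendance invalid?** Ordinary least squares was simulated on 12 monthly proportions with no true effect (3,000 runs per setting; monthly denominators averaging 20, or 10 in the most extreme setting). Type I error lay between about 3.5% and 5.8%, both for a simple before-after model and for the level change in a segmented model. In the segmented model at least one fitted value left 0–1 in about 5% of runs at 10% or 90% attendance, in none at 50%, and in 58% at 95% attendance with 10 per month. The denominators are assumptions.

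**6. Repeat tests.** From the article's Results: 531/446 = 1.19 elevated APRI tests per person and 985/816 = 1.21 for FIB-4. If all tests of one person shared one outcome and repeats were evenly spread, the variance would be understated by a factor of about 1.2, and the standard error by √1.19 to √1.21, about 9–10%.

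**The case against.** The strongest reply is that the authors wrote number where they meant proportion. The same sentence mentions the proportion of people with elevated scores who are referred, and the power section applies logistic regression to a referral proportion, so a referred/not-referred outcome does exist in the article. This is a likely explanation. It does not rescue the text, because that proportion is only to be described while the number is compared, and the objective is a monthly rate.

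Other replies stand in whole or in part:

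- A reader might infer that both models are wrong. Linear regression of proportions is a usable choice, and its type I error held in the check above.
- A reader might infer that both models contradict the power section. For referrals that section also says logistic, so the conflict is one of scale. For attendance the second clause could be read as detached from the logistic analyses, so the conflict is the natural reading but not a certain one.
- A reader might infer that test-level P values will be materially too small. Nothing says that repeat tests are treated as independent, and the plan states "Data will be analyzed per test event and per individual tested". This is a minor supporting point.
- The lack of allowance for volume applies to the count comparison only. Monthly test numbers and the referral proportion are also reported, so a change in volume would be visible.

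A further objection changes the remedy. Outcome Measures counts only referrals made through the online link. The comparator description says that referrals were faxed, and the link arrives with the intervention. On that definition the preintervention count is zero by construction, and a log-link step change has no finite estimate.

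**Conclusion.** The point holds in a limited form. The model named for the referral comparison does not fit the outcome as defined, and Analysis Methods and the Sample Size Justification do not describe the same analyses: count against proportion for referral, and linear against apparently logistic for attendance. This concerns stated text, not detail left to a fuller plan.

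Its size: the referral comparison cannot be run as written. The 1100 supports only a binary-proportion analysis, at a baseline that the article does not give. A 10% rise in testing would match the claimed detectable difference, provided that the 10% is relative, which the article does not say.

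A reader might infer that the published effect estimate would be uninterpretable. The article does not support that: a logistic fit to counts fails visibly and would be noticed. The harm is an unplanned choice of replacement model or outcome.

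**What to change.** 1. **Referral counts.** Analyse monthly referrals received by all routes, fax and online link, in both periods. Use a segmented quasi-Poisson or negative binomial model with log link, an offset for eligible individuals tested, and a step change at February 1, 2024 as the main term. Report online-link referrals descriptively for the intervention period only. If the referrer type is recorded, state whether specialist referrals are included, so that the count and the offset cover the same population as far as possible.
2. **Proportions.** Analyse referred among people with elevated scores, attended among referred, and linked among people with cirrhosis-range results by individual-level logistic or log-binomial regression on study period.
3. **Consistency.** Make Analysis Methods and the Sample Size Justification name the same outcomes and models. State the assumed baselines, and say whether the 10% and the 5% are relative or absolute.
4. **Minor.** Use person-clustered standard errors wherever the unit is the test event.

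Test numbers and referral numbers are already to be collected in both periods, so the cost is wording and a little more programming, with possibly wider intervals. All-route counting requires that faxed referrals be counted in the same way throughout. The article places the start of data analysis in August 2024, after the intervention period; the change should be fixed and dated before outcome data are examined.

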### Definitions

#### Comparator Group (Standard of Care)

Currently, APRI and FIB-4 scores are not routinely reported anywhere in Australia. Prior to the intervention, blood tests will be reported per standard of care. APRI and FIB-4 scores will be calculated automatically by the pathology service from the start of the study but will not be reported to ordering clinicians until the intervention period. FibroScans are requested through a paper-based referral form by general practitioners or specialists, which is then faxed to the hospital for triage and booking.

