### Study Timeline

#### Preintervention Period

Between August 1, 2023, and January 31, 2024, St Vincent’s Pathology will prospectively collect data on all ALT, AST, and platelet count test results conducted, and APRI and FIB-4 scores will be automatically calculated by the St Vincent’s Pathology data management system, but not reported to the ordering clinician. These data will be prospectively collected from St Vincent’s Pathology by a member of the study team, along with exposure variables outlined above. During the same time period, outcome measures per month will be prospectively collected from the St Vincent’s hospital electronic medical records by a member of the research team (number of FibroScan referrals, number [proportion] of scheduled FibroScan appointments attended, number [proportion] diagnosed with cirrhosis, and number [proportion] linked to specialist care).

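### The attendance analysis sets referred people with raised scores against pre-intervention appointments with no score restriction; separately, diagnosis and linkage use different cirrhosis definitions, so those steps do not chain

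*Protocol article*

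**What the plan says.** **Attendance.** In the Protocol article, Analysis Methods, the quantity of interest is "individuals with an elevated APRI or FIB-4 who are referred for a FibroScan and who attend their FibroScan appointment". It is to be "compared with the number (proportion) of FibroScan appointments attended prior to intervention", using linear regression. The Preintervention Period section lists the measure collected before the intervention as "number [proportion] of scheduled FibroScan appointments attended". The Sample Size Justification refers to "determining the proportion of FibroScan referrals that are attended". Neither of these last two is limited to people with a raised score.

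Objective 3 reads differently. It concerns "transient elastography tests performed in those with an elevated APRI and or FIB-4 score during the intervention period, compared with the preintervention period". Outcome Measures likewise lists the number and proportion of people with APRI above 1.0 or FIB-4 above 2.67 who have a FibroScan. The Comparator Group section makes such a comparison possible: "APRI and FIB-4 scores will be calculated automatically by the pathology service from the start of the study". The Results section adds that linkage of these scores to referral and attendance is under way.

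**Cirrhosis definition.** Outcome Measures counts the people scanned each month "who have cirrhosis diagnosed (liver stiffness measurement >12.5kPa". The linkage outcomes in the same list concern "individuals with etiology-specific cirrhosis range FibroScan results that are referred to the specialist liver clinic" and, with the same qualifier, attendance at that clinic. No etiology-specific cut-offs are printed.

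**The concern.** A before-after contrast needs the same quantity on both sides. As written, the attendance contrast changes the unit from people to appointments and drops the score restriction on the pre-intervention side. Pre-intervention FibroScans are requested by general practitioners or specialists, whereas the screened cohort excludes blood tests from inpatient stays and hospital outpatient services. An unrestricted appointment count can therefore include people who could never enter the screened cohort. If their attendance differs from that of screened people with raised scores, the analysis reports a change that reflects only who was counted.

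The second matter lies between steps, not between periods. The hypothesis is that both diagnosis and linkage will rise, so a reader will want to follow people from diagnosis to specialist care. That cannot be done if the diagnosed group and the linkage denominator are defined differently.

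**Working it through.** **1. The attendance texts side by side**

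| Section | Unit | Restricted to raised scores? |
|---|---|---|
| Analysis Methods, group described | People referred | Yes |
| Analysis Methods, pre-intervention comparator | Appointments | Not stated |
| Preintervention Period, data list | Scheduled appointments | Not stated |
| Sample Size Justification | Referrals | Not stated |
| Objective 3 | Tests performed | Yes, both periods |
| Outcome Measures, raised-score scanning | People | Yes |

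**2. The plan's own figure.** The Sample Size Justification claims 90% power for a 5% difference with 1100 per subgroup, and names attendance of referrals as one use. I read 5% as five percentage points. With two-sided alpha 0.05,

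n = [1.960·√(2·p̄·(1−p̄)) + 1.282·√(p1(1−p1) + p2(1−p2))]² / 0.05².

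For 13% against 18%, n = 1099. For 50% against 55%, n = 2095, and 1100 would give 65% power. The figure of 1100 is recovered only when the lower proportion is near 13% or near 82%. No baseline is stated, so the figure is neither confirmed nor refuted. It is used below only for the 5-point yardstick.

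**3. Size of a spurious attendance difference.** Let aE be attendance in people with a raised score, aO attendance in everyone else, and s the share of pre-intervention appointments held by people with a raised score. With no true change,

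apparent difference = aE − [s·aE + (1−s)·aO] = (1−s)(aE − aO).

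All three inputs are assumed, because the protocol gives none of them.

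| aE | aO | s = 10% | s = 30% | s = 50% |
|---|---|---|---|---|
| 80% | 75% | +4.5 | +3.5 | +2.5 |
| 80% | 70% | +9 | +7 | +5 |
| 70% | 80% | −9 | −7 | −5 |

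With the same raised-score group on both sides, the expected difference is 0.

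**4. Chance of a false signal.** A two-proportion test stands in here for the planned regression. With 1100 per side and no true change, it would be significant about 51% of the time at aE 80%, aO 75%, s 30%, and about 80% of the time at aE 80%, aO 70%, s 50%. With 200 per side these fall to about 13% and 22%. The smaller size matters: the interim pre-intervention count of people with either score raised is between 816 (full overlap) and 446 + 816 = 1262 (no overlap), or 2.2% to 3.3% of 37,872, and those referred are a subset.

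**5. The two cirrhosis definitions.** Let D be the people scanned with stiffness above 12.5 kPa, and E those in the etiology-specific range. The diagnosis outcome is the size of D. The linkage proportion is (linked within E) / (size of E). Multiplying the size of D by that proportion gives the number linked among those diagnosed only if D and E coincide or happen to have the same linkage rate. Neither is stated. The outcome for cirrhosis confirmed in people with raised scores states no threshold, so which definition it follows is also open. No numerical range can be given, because neither the etiology-specific cut-offs nor the stiffness distribution is printed.

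**The case against.** The strongest reply is that the protocol already contains the like-for-like comparison. Scanning among people with raised scores is a primary outcome, Primary Outcome Measurement says primary outcomes are compared with the preceding six months, and objective 3 says the same. The Analysis Methods sentence may simply be elliptical, with its opening subject meant to carry over. This stands in part. It shows that a matched comparison was probably intended, and it confines the problem to one step, attendance among those referred. It does not remove the problem, because the comparator clause, the data list and the power statement all omit the restriction.

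Three stronger readings are tempting, and the documents do not support them.

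- That the comparator is definitely every appointment at the clinic. The text gives no restriction; it does not say all.
- That having two cirrhosis definitions biases the before-after linkage contrast. If each is applied in the same way in both periods, it does not.
- That a move from fax to web forms changes how etiology is recorded and so shifts the linkage denominator. The web form is added to standard of care; no section says the fax form is withdrawn. Nor does any section say that the indication on the request assigns the etiology-specific range. It is listed only as a collected variable.

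**Conclusion.** The concern holds in two limited parts.

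First, the attendance comparison as written mixes units and drops the score restriction on the pre-intervention side, in conflict with objective 3 and the raised-score scanning outcome. Its effect is unknown. If attendance in the two groups differs by 10 points, and people with raised scores hold 10% to 50% of pre-intervention appointments, the artefact is 5 to 9 points in either direction, which equals or exceeds the 5-point target. With a 5-point gap it is 2.5 to 4.5 points. If attendance does not differ between the groups, this artefact is zero.

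Second, the diagnosed group and the linkage denominator follow different definitions, so these steps do not chain within a period. This is an inconsistency to reconcile, not a demonstrated bias. Nothing here implies that either definition is the right one.

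The change should be made before the analysis planned for August 2024.

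**What to change.** 1. In Analysis Methods and in the Preintervention Period data list, define attendance identically for both periods: among community-tested people with APRI above 1.0 or FIB-4 above 2.67 who were referred, the proportion who attended at least one FibroScan. Use the pre-intervention scores that are calculated but not reported.
2. Present this alongside the existing outcome, the proportion of all people with raised scores who were scanned. The intervention may change who is referred, so attendance among those referred should not stand alone.
3. In Outcome Measures, reconcile the cirrhosis wording so that one named definition serves both diagnosis and linkage, or report both definitions at every step. Either way, apply them identically in both periods and say which one governs the confirmed-cirrhosis outcome in people with raised scores.

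The cost is wording. The scores exist from the start of the study, and their linkage to referral and attendance is already in progress.

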#### Intervention Period

From February 1, 2024, to July 31, 2024, St Vincent’s Pathology will commence inclusion of automatic calculation of APRI and FIB-4 score reporting on all pathology blood testing events where an AST, ALT, and platelet count are ordered. St Vincent’s Pathology will provide for these testing events: (1) the APRI result, (2) the FIB-4 result, (3) an explanation of what APRI and FIB-4 measure and what cutoffs are used to define cirrhosis, and (4) recommendations for further investigation of elevated APRI or FIB-4 with transient elastography (FibroScan) and performance of a liver disease screen if underlying liver disease is not known. In addition, a web link to the St Vincent’s Pathology website for liver disease and cirrhosis information page will be included on all blood test reports where APRI and FIB-4 are calculated, with a provided URL link to a unique St Vincent’s Hospital FibroScan referral form. This link will be distinct from the standard fax-based St Vincent’s FibroScan referral form to allow measurement of referrals specifically generated in response to St Vincent’s Pathology APRI or FIB-4 score calculations during the study period.

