## Results

As of January 2024, in the preintervention phase of this study, a total of 120,972 tests were performed by the laboratory. Of these tests, 78,947 (65.3%) tests were excluded, with the remaining 42,025 (34.7%) tests on 37,872 individuals meeting inclusion criteria with APRI and FIB-4 being able to be calculated (Figure 1). Of these, 1.3% (n=531) had elevated APRI greater than 1 occurring in 446 individuals, and 2.3% (n=985) had elevated FIB-4 greater than 2.67 occurring in 816 individuals (Table 1). Linking these data with FibroScan referral and appointment attendance is ongoing and will continue during the intervention phase.

Data analysis is expected to begin following 6 months of intervention in August 2024, and the publication of results will then follow.

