**Figure 1 figure1:**
[figure not shown]
Flow diagram of current data from the preintervention period of blood tests performed at St Vincent’s Pathology and included in the interim analysis. ALT: alanine transferase; AST: aspartate transferase; FBC: full blood count; LFT: liver function test.

**Table 1 table1:** Proportion of blood tests and individuals with elevated Aspartate Transaminse–to-Platelet Ratio Index (APRI )and Fibrosis-4 (FIB-4) values.

	Total test events (n=42,025), n (%)	Individuals (n=37,872), n (%)
Elevated ALT^a^	16,760 (39.9)	15,285 (40.4)
Elevated APRI>1	531 (1.3)	446 (1.2)
Elevated FIB-4>2.67	985 (2.3)	816 (2.2)

^a^ALT: alanine transferase.

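### Cutoff-level accuracy is planned for APRI alone, although the programme flags people on APRI or FIB-4, so sensitivity, specificity and NPV of the rule in use would not be estimated

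*Protocol article*

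**What the plan says.** Under Intervention Period, the laboratory report carries "recommendations for further investigation of elevated APRI or FIB-4 with transient elastography (FibroScan"), so one elevated score of either kind is enough to prompt a scan. The fourth primary objective concerns "individuals with APRI greater than 1.0 or FIB-4 greater than 2.67 that have cirrhosis range median stiffness (kPa) confirmed on FibroScan". Outcome Measures lists the matching primary outcome: "the number (proportion) of individuals with an APRI greater than 1.0 or FIB-4 score greater than 2.67 who have cirrhosis confirmed by FibroScan". All three join the scores with 'or'.

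Analysis Methods opens the relevant sentence with the same group: "The number and proportion of individuals with an elevated APRI or FIB-4 who had cirrhosis confirmed by FibroScan will be described". The second half of that sentence then plans "sensitivity, specificity, and positive and negative predictive values of APRI for cirrhosis determined by confusion matrix", naming APRI only. The following sentence brings FIB-4 back: "The area under the receiver operating characteristic curve of APRI and FIB-4 for cirrhosis diagnosis will also be calculated". The APRI cutoff for the matrix is not restated there; 1.0 is taken from Objectives and Outcome Measures.

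**The concern.** Sensitivity, specificity and NPV describe a particular positive/negative rule. The rule that generates the programme's FibroScan recommendations is either-positive, but the rule in the confusion matrix is APRI alone. Someone with FIB-4 above 2.67, APRI of 1.0 or less and cirrhosis on FibroScan is a case the programme found, yet is a false negative in the planned matrix. Someone with the same scores and no cirrhosis used a FibroScan appointment on the programme's recommendation, yet is a true negative in that matrix.

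An area under the curve summarises ranking over all thresholds, so the FIB-4 analysis does not show how the 2.67 cutoff performs. The article says the study will determine the programme's effectiveness, and it names resources and referral logistics as limits on scaling up (Strengths and Limitations). Accuracy figures that a reader could attach to the programme should therefore describe the rule the programme applies. The mismatch is separate from the question of who gets scanned and would remain if everyone were.

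**Working it through.** **Inputs.** From Results and Table 1: 42,025 tests on 37,872 individuals; APRI >1 in 531 tests and 446 individuals; FIB-4 >2.67 in 985 tests and 816 individuals. The overlap between the two positive groups is not reported, so it is left free from 0 to 446 individuals (0 to 531 tests).

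**Reproducing Table 1.** Individuals: 446/37,872 = 1.18% and 816/37,872 = 2.15%, printed as 1.2% and 2.2%. Tests: 531/42,025 = 1.26% and 985/42,025 = 2.34%, printed as 1.3% and 2.3%. The figures agree.

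**Size of the group that APRI alone does not flag.** Let A be the number APRI-positive, F the number FIB-4-positive and V the overlap. The either-positive group is U = A + F − V, and the share of it with APRI at or below the cutoff is (U − A)/U.

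| Overlap assumed | U | APRI not elevated | Share |
|---|---|---|---|
| Individuals, full (446) | 816 | 370 | 45.3% |
| Individuals, half (223) | 1,039 | 593 | 57.1% |
| Individuals, none (0) | 1,262 | 816 | 64.7% |
| Tests, full (531) | 985 | 454 | 46.1% |
| Tests, none (0) | 1,516 | 985 | 65.0% |

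The lower bound needs no assumption about overlap, because overlap cannot exceed the smaller group. It applies to the laboratory cohort.

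**Direction of the difference among scanned people.** Among those with cirrhosis on FibroScan, let a have APRI elevated (with or without FIB-4), b have FIB-4 elevated only, and c have neither. Among those without cirrhosis, let d, e and f be the same three groups.

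- Sensitivity: APRI alone a/(a+b+c); either-positive (a+b)/(a+b+c). The difference is b/(a+b+c), which is never negative.
- Specificity: APRI alone (e+f)/(d+e+f); either-positive f/(d+e+f). The difference is e/(d+e+f), which is never negative.
- NPV: APRI alone (e+f)/(b+c+e+f); either-positive f/(c+f). The direction depends on whether cirrhosis is more frequent in the FIB-4-only group, b/(b+e), than in the group with neither, c/(c+f). It is not fixed in advance.

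So the APRI-only matrix equals or understates the sensitivity of the deployed rule, and equals or overstates its specificity. The documents give no values for a to f, so the size of these differences cannot be computed.

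**What each index test receives in Analysis Methods.**

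| Index test | Planned |
|---|---|
| APRI | Sensitivity, specificity, PPV, NPV; area under the curve |
| FIB-4 | Area under the curve only |
| APRI or FIB-4 elevated | Number and proportion with confirmed cirrhosis only |

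**The case against.** Four points can be made for the plan.

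1. The combined rule is not ignored. A reader might infer that it goes unevaluated and that its PPV is never estimated. The documents do not support this: the proportion of either-positive individuals with confirmed cirrhosis is an objective, a primary outcome and a planned analysis. With scanned people as the denominator, that proportion is the PPV. This objection stands and limits the gap to sensitivity, specificity and NPV, although the denominator should be stated.

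2. A reader might also infer that at least 45% of screen-positive people in the confusion matrix would be counted as test-negative. That does not follow. The 45% to 65% describes all either-positive people in the preintervention laboratory data. The matrix can contain only people with a FibroScan result, the study schedules no additional testing, and the mix of scores among those scanned is not given. If APRI-positive people are scanned more often, the share could be lower. This objection also stands.

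3. A matrix labelled as APRI is not wrong as a description of APRI. Accuracy is not among the listed objectives or outcomes, and the article elsewhere uses APRI as shorthand for a programme that reports both scores. The first part is fair: the analysis is ancillary, and no published figure would be false if labelled correctly. The shorthand reading is weaker, because the very next sentence names both scores for the area under the curve and the first half of the same sentence uses the either-positive group.

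4. Extra tables may be left to a fuller plan. That would answer an omission, but here the article names the index test, and the one it names differs from the rule in use.

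The first objective and the secondary outcomes join the cutoffs with 'and', which could suggest a third, both-positive definition. The natural reading is a list of two scores, as Table 1 shows them, so nothing is made of it.

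**Conclusion.** The point holds in limited form. As written, the plan yields no sensitivity, specificity or NPV for the either-positive rule that prompts FibroScan, and no cutoff-level measure for FIB-4 >2.67. The direction of the difference in sensitivity and specificity is certain among the same scanned people; its size is unknown. The potential for a material difference is shown by the laboratory cohort, where 45% to 65% of either-positive individuals are not APRI-positive, the range being due solely to the unreported overlap. The conclusion assumes that the matrix uses the APRI cutoff of 1.0 given elsewhere in the article. The pre-post comparisons of referral, scanning and linkage are unaffected. The change should be made, but it concerns an ancillary accuracy analysis and not the main comparison.

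**What to change.** In Analysis Methods, name APRI >1.0 or FIB-4 >2.67 as the index test for the main confusion matrix, and report sensitivity, specificity, PPV and NPV for it. Give separate matrices for APRI >1.0 alone and FIB-4 >2.67 alone, and keep the areas under the curve for both scores. State that the denominator for all three matrices is individuals with a FibroScan result, and state the denominator of the confirmed-cirrhosis proportion as well, so that readers can tell a PPV from a yield over everyone flagged.

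The cost is a change of wording and two further 2x2 tables. Both scores are already calculated for every included test, so no new data are needed and clinical management is untouched. The article places the start of data analysis in August 2024, so the wording can be settled before any accuracy result is seen.
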